## Abstract

**Background:**

Poor patient adherence to continuous positive airway pressure **(CPAP)** remains a common challenging issue and a major cause of treatment failure in patients with obstructive sleep apnea-hypopnea syndrome **(OSAHS)**. Our study aims to test the hypothesis that therapeutic patient education **(TPE)** combined with augmented clinical support **(ACS)** at CPAP initiation would improve CPAP adherence and treatment outcomes compared to usual care.

**Patients and methods:**

We will perform a prospective, randomized, controlled, parallel-group trial including 60 adult patients newly diagnosed with severe OSAHS. Each patient will be randomly assigned to either the TPE group or the usual care group and then scheduled to start CPAP therapy within 1–2 weeks after the nocturnal polygraph recording. For the TPE group, CPAP initiation will be performed at the hospital during a 3-hour educational session that will include 4 workshops entitled: “What’s OSAHS”, “CPAP machine: what is it? How does it work? And what does it serve for?”, “How to use your CPAP and fit your mask” and “How to deal with CPAP side effects”. The educational team will include a sleep disorders specialist, a sleep nurse, and a CPAP technician. As educational tools, we will use a short storytelling video in the local language, live demonstrations and a daily desk calendar with 60 removable sheets and 1 tip on CPAP therapy on each sheet. Patients assigned to the usual care group will undergo CPAP initiation at home under the guidance of a CPAP technician and will not receive additional educational support beyond the documents provided by the manufacturers.

Our primary outcome is unadjusted CPAP adherence measured in hours/night at 1, 3, and 6 months after CPAP initiation. Our secondary outcome is functional status at the 6-month follow-up, which included snoring, nasal obstruction symptoms, subjective quality of life, fatigue, emotional status, cognitive function, insomnia and excessive daytime sleepiness **(EDS)**.

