### 2.2. Patients

All patients referred to the Department of Respiratory and Sleep Medicine at Hedi Chaker University Hospital of Sfax-Tunisia, for suspected OSAHS will be screened for eligibility between January 2025 and July 2025. Sixty patients will be included. The study will be terminated by December 31^st^, 2025.

Patients will be determined eligible if they are aged 18 years old and above and newly diagnosed with severe OSAS (obstructive apnea-hypopnea index **(OAHI)** ≥ 30 events/ h) as revealed by an overnight type III polysomnography **(PSG)**.

Patients who have previously received CPAP therapy will not be included in the study. Additional exclusion criteria are refusal to participate, illiteracy, pregnancy, major mental disorders, severe heart failure with systolic fraction ejection **(SEF)** < 45%, severe neuromuscular diseases and oxygen supplementation.

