**2.3.4.1. CPAP therapy**

AirSense S10 (ResMed) will be used for all enrolled patients with a pressure range of 4 cm H2O to 20 cm H2O. Each patient will be sized for an appropriate nasal CPAP mask from ResMed. After 2 weeks of at-home auto-CPAP titration, a fixed CPAP prescription follows according to data downloaded from the secure digital **(SD)** card of the device. The 95th percentile **(p95)** of the pressure titrated by Auto-CPAP will be used as a reference pressure level for fixed-CPAP therapy.

Data from the CPAP SD card, including residual AHI; total and daily usage time and air leak, will be recorded using the ResScan software. Good adherence to CPAP at 3 months will be defined as a CPAP use for ≥4 h per night on ≥ 70% of nights within a consecutive thirty-day period anytime during the last 90 days of therapy. To assess patients’ perception of CPAP therapy on the morning following the first night of CPAP titration, we will use the Sleep Disorders Center CPAP Questionnaire **(SDC CPAP questionnaire)**. This self-administered questionnaire includes 6 items scored on a 10-point Likert scale, with responses ranging from 1 (no difficulty/no discomfort/positive attitude toward CPAP) to 10 (significant difficulty/significant discomfort/ negative attitude towards CPAP). We used the mean CPAP perception score to create 2 categories of patients: poor CPAP perception (scores > 16) and good CPAP perception (scores ≤ 16). We hypothesized that a poor CPAP perception score would independently predict poor CPAP adherence during the first 30 days of therapy. [7].

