**Nasal obstruction**

Chronic nasal obstruction is a common symptom among patients with OSAHS and is a known risk factor for OSAHS as well as CPAP intolerance and discontinuation. We will use a validated Arabic version of the Nasal Obstruction Symptom Evaluation **(NOSE)** scale to assess the impact of nasal obstruction on patients’ quality of life [8]. This scale is a reliable and valid self-report questionnaire comprising 5 items related to nasal obstruction symptoms experienced over the past month. Each item is scored on a 5-point Likert scale, where 0 indicates “not a problem” and 3 indicates a severe problem. The sum of the 5-item-answers is multiplied by 5, which provides a total score ranging from 0 to 100 with higher scores indicating worse symptoms. NOSE scores of [5–25], [26–50], and [50–100] represent mild, moderate, and severe nasal obstruction-related symptoms, respectively.

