### 2.6. Protocol study

After a nocturnal polygraph recording showed severe OSAHS, the patient will be seen by a sleep doctor the following day. The doctor will explain the diagnosis and the need for CPAP therapy. The patient will then complete an informed consent form to participate in the study and be randomly assigned to either the usual care (n = 30) or the TPE group (n = 30). Additionally, the patient will fill out a questionnaire covering sociodemographic data, health status, NOSE questionnaire, WHO-5 questionnaire, HAD questionnaire, FSS questionnaire, MoCA questionnaire, ESS questionnaire and ISI questionnaire. Following this, the patient will be scheduled to start CPAP therapy within 1–2 weeks after the nocturnal polygraph recording.

Following the TPE session, patients in the TPE group will be provided with CPAP devices to take home. They will be advised to call the sleep nurses if they experience any side effects. The phone line will be available on weekdays from 9:00 am to 4:00 pm, and patients can leave a message at other times. An assigned nurse will contact patients on the second and fifteenth days to identify and resolve any CPAP-related issues. The SDC CPAP Questionnaire will be administered by the nurse for each patient in this group on day 2 following CPAP titration.

Patients in the usual care group will be advised to consult the CPAP technician for any questions or concerns.

Both groups of patients will be scheduled for follow-up appointments with a CPAP technician and a sleep physician on day 15 (only if the CPAP perception score is poor) and at 1, 3, and 6 months after starting CPAP therapy. During each visit, we will assess adherence to and tolerance of CPAP by asking questions about side effects and reviewing CPAP SD Card data. Any CPAP-related issues reported by the patients will be addressed accordingly. At the 6-month follow-up, all patients will be asked to complete the functional outcomes questionnaires once again (Figs 1 and 2). Sleep physicians involved in the routine clinical follow-up of the patients will be blinded to each patient’s treatment group.

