### 2.7. Statistical analysis

The data analysis will be conducted using SPSS Statistics for Windows, Version 23.0 (IBM SPSS Statistics for Windows, Version 23.0. Armonk, NY: IBM). We will use the Kolmogorov-Smirnov test to assess the normal distribution of data. Continuous variables with a normal distribution will be expressed as mean and standard deviation **(SD)**, while non-normally distributed variables will be represented as median and interquartile range **(IQR)**. For comparing means of 2 and 3 or more categories of normally distributed continuous variables, independent Samples t-test and ANOVA test will be used, respectively. Medians of non-normally distributed continuous variables will be compared using non-parametric tests (Mann-Whitney U test and Kruskal-Wallis). Categorical variables will be presented as counts and frequencies. The frequencies of categorical variables will be compared using Pearson χ2 or Fisher’s exact test, as appropriate. A significant level of p < 0.05 will be considered.

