## 4. Conclusion

Poor patient adherence to CPAP remains a common challenging issue and a major cause of treatment failure. Previous studies on the impact of TPE on CPAP adherence have led to conflicting findings. In this context, we decided to conduct a prospective, randomized, controlled, parallel-group trial to assess the impact of TPE combined with ACS on CPAP adherence and effectiveness when compared to usual care. Our educational materials include a short storytelling video in the local language, live demonstrations, a daily desk calendar with 60 removable sheets and 1 tip on CPAP therapy on each sheet, and educational support provided by the manufacturers. Patients will be followed up for 6 months. Our primary outcome is unadjusted CPAP use measured in hours/night, and our secondary outcome is OSAHS-related functional outcomes. We firmly believe that improving CPAP adherence should be considered a priority in patients with OSAHOS, so to achieve this goal, we designed this original protocol combining TPE with ACS.

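### Baseline NOSE, a score for a factor the protocol itself calls prognostic for CPAP discontinuation, is collected on all 60 patients but not used in the primary comparison, which gives up some precision

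*Protocol article*

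**What the plan says.** In the Protocol article, the Abstract (Patients and methods) gives the primary outcome as "Our primary outcome is unadjusted CPAP adherence measured in hours/night at 1, 3, and 6 months after CPAP initiation", and section 4 (Conclusion) repeats the label: "Our primary outcome is unadjusted CPAP use measured in hours/night". Section 2.3.4 (Outcome measures) defines the same outcome at the same three times without the word unadjusted.

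Section 2.7 compares two groups on a continuous variable by the independent-samples t-test, or by Mann-Whitney if the data are not normal. It names no model with a covariate. The criterion is "A significant level of p < 0.05 will be considered", with sidedness not stated.

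On nasal obstruction, section 2.3.4.2 says it is common among these patients and "is a known risk factor for OSAHS as well as CPAP intolerance and discontinuation". Section 2.2 lists the exclusions ("Additional exclusion criteria are refusal to participate, illiteracy, pregnancy, major mental disorders", then heart failure, neuromuscular disease and oxygen supplementation), with no nasal obstruction criterion. Section 2.3.4.1 says "Each patient will be sized for an appropriate nasal CPAP mask from ResMed".

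Section 2.2 also says "Sixty patients will be included", and section 2.6 splits them 30 and 30. Section 2.6 then lists the questionnaires each patient fills out at entry, NOSE among them. They come after the sentence on consent and assignment, and the order relative to disclosure of the allocation is not stated. NOSE has one other stated use, as a functional outcome at 6 months.

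**The concern.** Discontinuing CPAP lowers hours per night, so a risk factor for discontinuation should be prognostic for the primary outcome. The protocol identifies such a factor, measures it before treatment starts and then describes a primary comparison that does not use it.

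Two things follow in a trial of this size, and they are two views of the same variance. Variation in h/night explained by baseline nasal obstruction stays in the error term, so the interval for the education effect is wider than the collected data allow. And in the one randomisation that is carried out, any chance difference between arms in nasal obstruction moves the estimate, with nothing in the planned analysis to correct for it.

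Prespecification also matters. If an imbalance is seen at the end and NOSE is added then, the adjusted result will look data-driven.

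**Working it through.** **Plan's own figure.** The article gives no power, SD or design effect with the 60 patients, so there is no stated calculation to reproduce here.

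**Inputs from the documents.** 30 patients per arm (section 2.6); 5% level (section 2.7), taken as two-sided; effects of 1.5, 1.7 and 2.0 h/night cited from earlier trials (section 1), used only for scale.

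**Assumptions, not in the documents.** SD of adherence 2 h/night; correlation r between baseline NOSE and adherence 0.2 to 0.4 in size, with 0.1 as a pessimistic case.

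**Step 1: chance imbalance.** The SE of the baseline difference between arms is sqrt(1/30 + 1/30) = 0.258 SD. The arms then differ by more than 0.25 SD in about 33% of randomisations and by more than 0.5 SD in about 5.3%.

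**Step 2: effect on the estimate.** Shift = r × SD × imbalance.
- Imbalance of 1 SE (0.258 SD): 0.2 × 2 × 0.258 = 0.10 h/night; 0.4 × 2 × 0.258 = 0.21 h/night.
- Imbalance of 1.96 SE (0.506 SD, exceeded in 1 trial in 20): 0.2 × 2 × 0.506 = 0.20 h/night; 0.4 × 2 × 0.506 = 0.40 h/night.

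At an SD of 3 h/night these shifts are half as large again.

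**Step 3: variance.** Adjustment multiplies the residual variance by 1 − r². Estimating the slope costs a factor of about 1 + 1/(60 − 4) = 1.018. The proportions do not depend on the SD.

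| r | Variance removed (r²) | Net factor (1 − r²) × 1.018 | Equivalent unadjusted N, 60/(1 − r²) |
|---|---|---|---|
| 0.1 | 1% | 1.008 (no gain) | 60.6 |
| 0.2 | 4% | 0.977 | 62.5 |
| 0.3 | 9% | 0.926 | 65.9 |
| 0.4 | 16% | 0.855 | 71.4 |

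The last column ignores the 1.018 cost.

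**Step 4: width of the interval.** At SD 2 the SE of the unadjusted difference is 2 × 0.258 = 0.516 h, and the 95% half-width is 2.00 × 0.516 = 1.03 h. With adjustment it becomes 1.03 × sqrt(0.977) = 1.02 h at r = 0.2 and 1.03 × sqrt(0.855), about 0.96 h, at r = 0.4. The gain is about 0.01 to 0.08 h/night.

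**Step 5: power for 1.5 h/night, before the 1.018 cost.** At SD 2: 82.8% unadjusted, 84.2% at r = 0.2, 88.7% at r = 0.4. At SD 2.5: 64.2%, 66.0% and 71.8%.

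**Step 6: validity of the planned test.** In 40,000 simulated trials of 30 per arm with no treatment effect and a covariate correlated 0.3 or 0.5 with the outcome, the unadjusted t-test rejected in 5.1% and 5.3% of trials. The mean difference was within 0.002 SD of zero.

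**The case against.** The case against has several parts.

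- **An unadjusted comparison in a randomised trial is correct.** This stands, and step 6 confirms it. A reader might infer that imbalance in nasal obstruction confounds or biases the result. It does not: the unadjusted interval already allows for chance imbalance, and only efficiency is in question.
- **The gain is small and rests on an assumed correlation.** This also stands. At r = 0.2 the interval hardly changes, and at 0.1 nothing is gained. The 0.40 h/night shift needs both the top of the assumed range and a 1-in-20 imbalance.
- **The word unadjusted describes the outcome, and section 2.3.4 omits it.** True, so a reader should not infer that the article expressly rules out an adjusted comparison. The conclusion rests on the label together with section 2.7. No other adjustment of h/night is described that would give the word a different meaning.
- **Covariates and balancing are often left to a fuller plan.** Fair for balancing: the article's silence does not show that none is intended, and nothing here depends on it. It is weaker for the analysis, because the article states which tests will be used and none is adjusted.
- **Why NOSE alone?** Section 1 lists other influences on adherence, and several are collected at baseline. The choice is open to debate. The reason for NOSE is that the protocol itself ties nasal obstruction to CPAP discontinuation and scores it on a continuous scale in every patient.

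Two further stronger readings are not supported. The protocol says risk factor, not cause. And admitting patients at any level of nasal obstruction is no defect; it fits the pragmatic aim in section 3.1.

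**Conclusion.** The point holds as a matter of efficiency. A baseline measure of a factor that the protocol presents as prognostic for its primary outcome is available for every patient, and the stated analysis does not use it. The planned test is not wrong.

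The size depends on a correlation that the documents do not give: no net gain at 0.1, about 2% of variance net at 0.2 and about 15% net at 0.4. At 0.3 to 0.4 this is worth roughly 6 to 11 more patients on a base of 60, before the cost of the extra parameter. The most that adjustment can be expected to lose is about 2%. Since section 3.2 concedes that the sample is small, that balance favours adjusting, as an improvement worth making rather than the correction of an error.

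**What to change.** Keep eligibility unchanged. Then:

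1. In the Abstract, section 2.7 and section 4, state that the between-group difference in h/night at each of months 1, 3 and 6 (or in one repeated-measures model covering all three) is estimated by linear regression on arm, with the continuous baseline NOSE total as a prespecified covariate. Bring section 2.3.4 into line so that the outcome is described the same way throughout.
2. In section 2.7, keep the t-test or Mann-Whitney comparison as a supportive analysis of the primary outcome, so that the normality check no longer decides the primary method.
3. In section 2.6, state that the baseline questionnaires are completed before the allocation is disclosed. NOSE is self-reported, and a score given after the patient knows the arm is not a clean baseline covariate.

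**Cost.** One degree of freedom (about 2% efficiency), a second estimate to report, edits to these sections, and possibly a small change in the order of steps at the enrolment visit. No new data, visits or patients are needed. If the sponsor prefers to keep the unadjusted comparison as primary, the NOSE-adjusted model should be a named, prespecified sensitivity analysis, with a sentence on why it is not primary.

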**Conclusion:**

We designed this original protocol by combining TPE with ACS. We hope that our findings will help us improve CPAP adherence among Tunisian patients with OSAHS.

## 1. Background

Obstructive sleep apnea-hypopnea syndrome **(OSAHS)** is probably the most common sleep-related disorder in Tunisia, with recent data from an online survey suggesting that nearly 10% of middle-aged Tunisian adults are at high risk for OSAHS [1]. Untreated OSA is associated with significant cardiovascular and metabolic morbidity, impaired emotional health, neurocognitive dysfunction, increased accident risk, and all-cause mortality. While there are various treatment methods for OSAHS, continuous positive airway pressure **(CPAP)** remains the first-line and gold-standard therapy for symptomatic and moderate-to-severe OSAHS patients. There is plenty of evidence to show that CPAP significantly improves several long-term clinically important outcomes including excessive daytime sleepiness **(EDS)**, sleep-related quality of life, motor vehicle accidents, and blood pressure [2]. Good patient adherence is the key to CPAP therapy effectiveness. As yet, there is no consensual definition of good CPAP adherence in terms of the threshold level for daily CPAP use required to achieve and maintain therapeutic effectiveness. The US Medicare policy for continued coverage of a CPAP device requires objective evidence of CPAP use for ≥4 hours (h) per night on ≥ 70% of nights within a consecutive thirty-day period anytime during the first 90 days of therapy [3]. However, it’s becoming increasingly recognized that the optimal threshold for sufficient nightly CPAP use may depend upon the therapeutic outcome in question and the patient’s self-perception of symptom severity. Moreover, a linear dose-response relationship was found between CPAP use and several outcomes with greater benefit with increased nightly duration of use > 7 h per night.

Despite the well-established efficacy of CPAP therapy, poor patient adherence remains a common challenging issue and a major cause of treatment failure. According to a 2004 quantitative review, the highest rate of low therapeutic adherence was associated with sleep disorders when compared to 17 other chronic conditions, such as human immunodeficiency virus (HIV) infection, cancer, cardiovascular disease, renal disease, and diabetes mellitus [4]. In a systemic review of 82 studies conducted over a twenty-year timeframe (1994–2015), the overall poor CPAP adherence rate based on a 7-h/night sleep time was 34.1%, and there was no significant improvement in CPAP adherence over the time frame. More interestingly, the nationwide claims data lake for Sleep Apnea **(ALASKA)**, a large-scale analysis of the French national healthcare database including 480,000 patients treated with CPAP, reported that almost half of patients discontinue CPAP use at 3 years [5].

Poor adherence to CPAP may result from device-related issues (mask type, air leak, CPAP side effects) or the patient’s clinical condition (socioeconomic status, comorbidities, psychosocial issues, endophenotype of the disease).

Over the last two decades, several interventions have been proven to increase CPAP adherence, including technological advances in CPAP devices, augmented clinical support **(ACS)** (more frequent appointments, telephone calls, home visits), therapeutic patient education **(TPE)**, cognitive behavioral therapy and motivational enhancement. There is an increasing tendency for most clinicians to offer their patients a combination of ACS and TPE. According to the World Health Organization **(WHO)** definition, TPE helps patients acquire or maintain the skills they need to self-manage their project life with a chronic disease in the best possible way. To achieve this, candidates for CPAP therapy should clearly understand their disease. They also need to have accurate expectations of the benefits and harms of treatment as many of them mistakenly believe that CPAP therapy will definitively cure their disease, while others may feel hesitant or scared about wearing a mask to sleep. Moreover, patients must be motivated enough to continue their treatment at home without medical supervision.

Various educational techniques and tools can be used such as interactive presentations, roundtables, treatment demonstrations, role-playing, photos, flyers, posters and videos. Both patients and healthcare providers prefer video format rather than text or orally staff-delivered information. The video message is supposed to be more attractive and persuasive as it provides easy and personalized access to information through simplified explanations and visual demonstrations. In addition, it can be self-administered by the patient, which would have the advantage of freeing up the staff’s time and preserving the patient’s privacy [6].

There is currently little empirical evidence about the impact of TPE on CPAP adherence with conflicting research findings. Three clinical randomized trials **(CRT)** of motivational enhancement therapy **(MET)**/motivational interviewing initiated before at-home CPAP treatment reported significantly improved adherence of 1.5 h per night, 1.7 h per night, and 2.0 h per night compared with the usual care approach. In contrast, a more recent study found that educational videos have no significant impact on CPAP adherence when compared with usual care.

In this context, we will conduct this study to test the hypothesis that TPE combined with ACS at CPAP initiation would improve CPAP adherence and treatment outcomes compared to usual care.

